## Abstract

**Background:**

Heroin-assisted treatment (HAT) is a proven effective treatment option for individuals with severe opioid use disorder (OUD). In Switzerland, pharmaceutical heroin (diacetylmorphine, DAM) is available in tablet form or as injectable liquid. This creates a large barrier for individuals who require the rapid onset of effect but are either unable or do not want to inject, or who primarily snort opioids. Early experimental data has demonstrated that intranasal DAM administration can be a viable alternative to the intravenous or intramuscular route of administration. The purpose of this study is to assess the feasibility, safety, and acceptability of intranasal HAT.

**Methods:**

This study will assess intranasal DAM using a prospective multicentre observational cohort study design in HAT clinics across Switzerland. Patients will be offered to switch from oral or injectable DAM to intranasal DAM. Participants will be followed-up over 3 years, with assessments at baseline, and after 4, 52, 104 and 156 weeks. The primary outcome measure (POM) is retention in treatment. Secondary outcomes (SOM) include prescriptions and routes of administration of other opioid agonists, illicit substance use, risk behaviour, delinquency, health and social functioning, treatment adherence, opioid craving, satisfaction, subjective effects, quality of life, physical health, and mental health.

**Conclusions:**

The results derived from this study will generate the first major body of clinical evidence on the safety, acceptability, and feasibility of intranasal HAT. If proven to be safe, feasible and acceptable, this study would increase the accessibility of intranasal OAT for individuals with OUD globally as a critical improvement in risk reduction.

## Introduction

Heroin-assisted treatment (HAT) is an established and effective treatment option for individuals with opioid use disorder (OUD) that do not respond to conventional opioid agonist treatment (OAT), namely methadone, buprenorphine and slow-release oral morphine [1, 2]. HAT includes the supervised provision of oral or injectable (intravenous; IV) pharmaceutical heroin (diacetylmorphine, DAM). HAT recognises that some patients require a rapid onset of opioid effects, in particular euphoria, which is associated with the subjective experience of a “rush” or “high” [3].

However, currently available routes of DAM administration (IV, oral) are increasingly insufficient in an aging user population. In Switzerland, individuals with OUD, including HAT patients, are ageing [4, 5]. With age and a long history of controlled IV DAM use or uncontrolled IV illicit opioid use, the state of access-veins deteriorates. As such, patients that are no longer able to inject DAM into peripheral veins due to deterioration either revert to injection in the inguinal veins/groin [6], to intramuscular injection, subcutaneous injection or change to oral DAM tablets. All these alternatives may be associated with reduced treatment outcomes. For instance, groin injections have been associated with complications such as deep vein thrombosis, mis-injection into artery or nerve, aneurism or severe infections and abscesses [6]. Similarly, subcutaneous (SC) and intramuscular (IM) injections have been related to possibly life-threatening injection-related injuries and diseases [7, 8]. Clinical experience shows that IM or SC injection is associated with complications such as infections and abscesses, indurations or skin lesions and is often described as painful [4, 9]. Furthermore, onset of effect and subjective “flash” are usually described as slower and less strong when injecting IM or SC. Both may also be contraindicated for persons on oral anticoagulation because of the risk of bleeding and haematoma. Alternatively, switching from IV DAM to oral DAM treatment is associated with fewer complications. However, oral DAM has a much slower absorption, lower bioavailability and less-strong onset of effect than IV but also IM and likely SC injecting [10–12]. It therefore produces only a relatively mild “rush” or euphoria, which renders oral DAM undesirable for many HAT patients.

Currently available routes of DAM administration (IV and oral) are also increasingly insufficient due to changing patterns of substance use. In Switzerland and the EU, intranasal use is increasing, while inhalation and injection are decreasing [13, 14]. Given the current treatment options, individuals who are using opioids intranasally and entering HAT are prescribed oral DAM. A prescription of injectable DAM for non-injecting patients would ethically be unacceptable due to the higher risks associated with this route of administration. However, as previously mentioned, oral DAM has a much slower onset and less subjective effects. Hence, it often has limited efficiency in this patient group and may lead to treatment drop-out, ongoing illicit substance use, diversion of DAM tablets and delinquency. Some patients that would otherwise qualify for HAT and mainly use illicit opioids intranasally may even be discouraged from entering HAT for these aforementioned reasons [4].

In order to address these clinical gaps, minimise harm, and improve treatment outcomes, a novel route of DAM administration (intranasal; IN) has been developed as an alternative to IV or oral DAM for patients in HAT. It has a similar onset of effect as IM administration and is thus likely to produce the desired “rush” [15–17]. Currently prescribed off-label in a small number of HAT patients, it seems to be associated with less adverse effects than IV, IM or SC injection and has been suggested as a harm reduction measure to reduce HCV infection rates [18, 19]. Intranasal HAT (n-HAT) was first described in a case-series and was suggested as an important risk-reduced rapid-onset alternative to other forms of HAT [20]. In a recently published case-report, IN DAM administration improved treatment adherence and health outcomes in a patient who craved the fast onset of effect of DAM but was unable to inject intravenously [19]. Similarly, patients in HAT comparing a one-off administration of IN DAM with IV DAM reported advantages for IN administration such as ease and convenience of use, avoidance of needle hazards, and reduced stigma [15]. Finally, overdose from nasal use occurs much less often than from IV use [21].

Few studies have investigated the pharmacokinetics and pharmacodynamics of IN DAM. However, these were conducted in pain patients [22, 23], “healthy” subjects with a history of heroin use but abstinent from opioids at the time of study [24, 25], and opioid-dependent subjects in oral OAT [17, 26] in doses much lower than those prescribed in HAT. Nevertheless, these studies demonstrated that after administration of IN DAM, considerable peak plasma concentrations of DAM and its metabolites are reached at a similar rate than IM administration [15, 17, 24, 25, 27]. One study that investigated the effects of 40 mg IN DAM versus 40 mg IV DAM in HAT patients suggests IN DAM to be effective in suppressing opioid withdrawal and acceptable to patients, if not preferable to injected use [15]. IN DAM has also been studied in paediatric pain patients, where it has been shown to be safe and effective [28].

To date, no study has investigated the clinical use of IN DAM in OAT. Despite the case report and case-series, n-HAT has never been systematically evaluated in a clinical study. To thoroughly evaluate the feasibility, safety, and acceptability of n-HAT, the first large-scale prospective multicentre observational study was developed.

## Methods

### Study design

The study is designed as an exploratory prospective multicentre clinical cohort study. Every HAT centre in Switzerland was invited to participate and 18 confirmed their participation. Given that there are 23 specialist outpatient centres offering HAT in Switzerland, this study is representative of the treatment system [29]. Within this treatment system, these outpatient centres provide HAT to around 1600 patients, which has been relatively constant within the last two decades [30]. Enrolled participants will switch from oral or injectable DAM (treatment as usual arm) to intranasal DAM. Follow-up will occur over three years, with assessments at baseline (t0), and after 4 (t4), 52 (t52), 104 (t104) and 156 (t156) weeks. These timepoints are standard follow-up periods when measuring retention in OAT [31]. Specifically, the first 4 weeks in OAT are particularly important as the risk of mortality is elevated when compared with the remainder of time receiving OAT [32]. Long-term retention in HAT has also been studied at similar time points (e.g., 2 years in Germany, 2 years in Spain, 4 years in the Netherlands) [33–35].

Participants in n-HAT will receive Diaphin^®^ IV 100 mg/ml (DiaMo Narcotics, Thun), approved in Switzerland for IV treatment of OUD in the HAT setting. It will be administered into the nostrils with a mucosal atomisation device (Fig. 1). Atomisers are personalised, disinfected following each administration and replaced every 7 days. Just like conventional treatment with IV and IM DAM, long-acting oral opioids such as methadone or and slow-release oral morphine can be used as additional medication in order to prevent withdrawal. Participants will also be allowed to combine nasal with oral, IV and IM DAM. The dosing of IN DAM and of DAM through other routes of administration will remain an individual decision of patients and prescriber. Therefore, patients will not receive the same dosification, but rather receive an IN DAM dosification that align with their needs. There is no limitation on concomitant opioid and/or non-opioid medication to be prescribed. This study design is meant to be as comparable to the current Swiss HAT setting as possible.

**Fig. 1 Fig1:**
[figure not shown]
Barrel and mucosal atomisation device for IN DAM administration

This research project will be conducted in accordance with the study protocol, the Declaration of Helsinki [36], the principles of Good Clinical Practice (GCP), the Human Research Act (HRA) and the Human Research Ordinance (HRO) [37] as well as other locally relevant regulations. The study protocol received ethical approval from all responsible ethics committees. The study will be conducted in accordance with all applicable regulations and GCP-related guidelines.

### Study objectives and hypotheses

The study aims at investigating whether IN DAM is clinically feasible, acceptable to patients, and safe to use in HAT. The primary outcome measure (POM) is retention in HAT with the IN DAM route of administration after 4 weeks, 52 weeks, 104 weeks and 156 weeks. The secondary outcome measures (SOM) are prescriptions and routes of administration of other opioid agonists, illicit substance use, risk behaviours, delinquency, health and social functioning, treatment adherence, craving for opioids and other substances, satisfaction with prescribed opioid, subjective effects, quality of life, physical health, and mental health.

We hypothesise that patients receiving IN DAM in HAT will be retained in treatment with this route of administration over short and long time periods. Furthermore, patients are expected to report high satisfaction within IN DAM. Thirdly, we hypothesise IN DAM to be safe, the number of prescribed injection events to decrease and use of illicit opioids to decline.

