### Study procedures

Participants will be recruited only after the decision for nasal DAM is made by the participants and the responsible physician independently from study procedures. Patients will be informed that study participation is voluntary, that they may withdraw from the study at any time and that withdrawal of consent will not affect their subsequent medical assistance and treatment. Patients will be given at least a day to consider participation in the study. Study procedures comprises of assessments with questionnaires and structured interviews at baseline, 4, 52, 104, 156 weeks, and of a duration around one hour each. These are described below and in Table 1.

**Table 1 Tab1:** Study assessments

*Study periods*	*Assessment 1 (Baseline)*	*Assessment 2*	*Assessments 3, 4 and 5*
*Time (weeks)*	*0*	*4*	*52, 104, 156*
*Inclusion/Exclusion Criteria*	*X*		
*Written Informed Consent*	*X*		
*Patient characteristics*	*X*		
*Medical History*	*X*		
*Retention*^*a*^	*X*	*X*	*X*
*Opioid agonist prescription*^*a*^	*X*	*X*	*X*
*Treatment adherence*^*a*^	*X*	*X*	*X*
*Frequency of visits*^*a*^	*X*	*X*	*X*
*Treatment Outcomes Profile (TOP)*^*b*^	*X*	*X*	*X*
*Health section of Opiate Treatment Index (OTI)*^*b*^*, including nose-related problems*	*X*	*X*	*X*
*Symptom-Checklist 27 (SCL-27)*^*b*^	*X*	*X*	*X*
*Adverse Events*^*b*^	*X*	*X*	*X*
*Opioid Agonist Scale*^*1,c*^	*X*	*X*	
*VAS Subjective effects*^*2,c*^	*X*	*X*	
*VAS Craving*^*c*^	*X*	*X*	*X*
*VAS Satisfaction*^*c*^	*X*	*X*	*X*

^1^20–30 min after DAM application

^2^10 min after DAM application

^a^Used to assess feasibility of IN DAM

^b^Used to assess safety of IN DAM

^c^Used to assess acceptability of IN DAM

Patients will remain in the study if they change route of administration of DAM and will continue assessments even if they no longer receive IN DAM until study completion after three years. Patients who switch from IN DAM to another DAM route of administration and subsequently switch back to IN DAM will be allowed to do so, as it is an observational study of clinical procedures. Short-term switches to other forms of DAM or OAT due to external circumstances such as vacations abroad (where DAM cannot be taken), illness, hospitalisations or similar will be considered as continuous IN treatment, as the basic prescription will not change. If a patient switches to another route of DAM administration as per prescription, this will be systematically assessed, and a change back to IN DAM as well.

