### Secondary outcome assessment

Opioid agonist prescriptions including substance, galenics, dose and route of administration in the past 4 weeks will be assessed using patient’s the medical charts at each time point (t0, t4, t52, t104, t156).

Adherence to treatment and frequency of visits in the past 4 weeks will be assessed using the recorded scheduled and realised dispensings in the patient’s medical charts at each time point (t0, t4, t52, t104, t156).

Illicit substance use, delinquency, health and social functioning and quality of life will be assessed by the Treatment Outcome Profile (TOP) at each time point (t0, t4, t52, t104, t156). The TOP is a 20-item instrument which assesses substance use, injecting risk behaviour, and crime by self-report in the past 4 weeks [38]. Quality of life and social functioning will be assessed using the proposed 0-to-20-point scale of the TOP at each time point (t0, t4, t52, t104, t156).

Opioid craving in the past 7 days will be measured by visual analogue scales (VAS) at each time point (t0, t4, t52, t104, t156). Craving for alcohol, benzodiazepines and cocaine will be measured likewise. Acceptability of nasal DAM will be assessed by VAS on satisfaction with the different routes of administrations in DAM. Additionally, questions on the willingness to continue with the current prescription will be asked.

Subjective DAM effects will be measured by visual analogue scales (VAS) twice (t0 and t4), 10 min after DAM application. The VAS presents the participant a rating scale which represents the spectrum of “opioid high”, heroin-typical effects, good effects, bad effects, pleasure and feeling unwell: the left end indicates “none” while the right end indicates “extreme” effects.

Furthermore, subjective effects of opioids will be assessed using the self-reported German version of the Opioid Agonist Scale at baseline and 4 week follow-up point (t0 and t4) [39]. Between 20 and 30 min after DAM administration, participants will rate the extent to which they experienced each of 16 morphine-like symptoms on a five-point scale from “not at all” to “extremely”.

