Physical health in the past 4 weeks will be assessed using the health section of the Opiate Treatment Index (OTI) at each time point (t0, t4, t52, t104, t156) [40]. Only the health section of the OTI will be used; the physical health section of the OTI is composed of items addressing signs and symptoms in major organ systems and injection-related health problems. An additional self-designed section regarding nose-related problems will also be included, inquiring for stuffed and/or runny nose, nasal burning or itching, nasal pain, nasal bleeding, alterations of smell or other problems.

Self-reported mental health symptoms in the last 7 days will be assessed using the Symptom-Checklist 27 (SCL-27) at each time point (t0, t4, t52, t104, t156). The SCL-27 is the short German version of the 90-item SCL-90 [41]. The SCL-27 is a commonly used reliable and valid instrument, consisting of six subscales and a general score.

Although this is an observational study and not a randomised controlled trial and the decision on which routes of administration will be used for DAM remains with clinicians and patients, we will assess safety with several different measures. First, study physicians will report any serious adverse events (SAEs) followed by immediate information of all study centres. Second, we will assess physical health and especially nasal health with the health section of the OTI and self-designed questions on nasal symptoms. Third, we will assess risk behaviour such as number of injection events inside and outside of treatment. AEs and SAEs are defined in the “Safety” section.

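### The injection hypothesis counts prescribed injections only: for participants coming from injectable DAM a fall largely restates the switch, and it cannot show whether injecting moves outside treatment

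*Protocol article*

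**What the plan says.** Study objectives and hypotheses gives the third hypothesis three limbs: "we hypothesise IN DAM to be safe, the number of prescribed injection events to decrease and use of illicit opioids to decline". The injection limb names prescribed events only. It sets no size of decrease and no population.

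The exposure is itself a change of prescribed route. Study design states: "Enrolled participants will switch from oral or injectable DAM (treatment as usual arm) to intranasal DAM". Study procedures places that change before entry: "Participants will be recruited only after the decision for nasal DAM is made by the participants and the responsible physician independently from study procedures". The switch need not be complete, because Study design adds: "Participants will also be allowed to combine nasal with oral, IV and IM DAM". Study procedures also lets participants leave and return to the nasal route while remaining in follow-up.

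Elsewhere the article plans broader measurement. Under Secondary outcome assessment, the safety paragraph says "we will assess risk behaviour such as number of injection events inside and outside of treatment". The Treatment Outcomes Profile (TOP), given at all five time points, "assesses substance use, injecting risk behaviour, and crime by self-report in the past 4 weeks". The listed secondary outcomes include "prescriptions and routes of administration of other opioid agonists, illicit substance use, risk behaviours, delinquency".

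**The concern.** An outcome is informative when it can move independently of the condition for entering the study. Here the two overlap. A participant from injectable DAM is enrolled because the prescription is moving to the nasal route, and the hypothesis is then that prescribed injections fall.

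The question for harm reduction is whether injecting as a whole falls or part of it moves outside the clinic. The article's own reasoning makes such a shift plausible. The Introduction likens nasal onset to intramuscular onset and describes the intramuscular effect as slower and weaker than the intravenous one. For oral DAM, it links slower onset and weaker effect to continued illicit use. The prescribed count is blind to a shift of this kind. A reported fall in prescribed injections could be read as reduced risk when it mainly describes what was prescribed.

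**Working it through.** The article gives no figure for this hypothesis, so there is none to reproduce. The check compares sections and then uses two illustrations whose rates are assumptions.

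**1. The sections side by side**

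- Hypothesis: prescribed injections only.
- Safety measure: injections inside and outside treatment.
- Entry: the decision for the nasal route comes first.

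The hypothesis therefore uses one of the two components that the safety measure uses, and it is the component that the entry decision acts on directly.

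**2. What the prescribed count can register**

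Assume 2 prescribed injections a day, none outside treatment at baseline, and full replacement by nasal DAM. Over 4 weeks the baseline count is 2 × 28 = 56. If a share c of these is replaced by injections outside treatment, the change in the total is -56 + 56c.

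| c | Change in prescribed count | Change in total count |
|---|---|---|
| 0 | -56 | -56 |
| 0.5 | -56 | -28 |
| 1.0 | -56 | 0 |
| 1.2 | -56 | +11.2 |

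At group level, with the same baseline:

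- If 30% inject outside treatment once a day, outside injections average 0.30 × 28 = 8.4 per person. The total is 8.4/56 = 15% of baseline, a fall of 85%.
- If all do so, outside injections average 28. The total is 28/56 = 50% of baseline, a fall of 50%.

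The prescribed count reads -100% in both cases.

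**3. How nearly automatic a fall is**

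I used a one-sided exact sign test at 0.025 on the direction of each participant's change in prescribed injections, with the number who change fixed at its expected value. This test is a device of mine and is not the planned analysis. The inputs are:

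- N = 100 or 200, the recruitment range in Sample size and power calculation;
- f, the share with prescribed injections at baseline (not given; assumed);
- s, the share of these who reduce (assumed 0.5, 0.8 or 1.0);
- g, the share of the others who start prescribed injections (assumed 0, 0.05 or 0.10).

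Expected decreases are N·f·s and expected increases are N·(1−f)·g. For example, N = 100, f = 0.2, s = 0.8 and g = 0.05 give 16 decreases and 4 increases, and a probability of 0.804 of a significant fall.

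With g = 0 every change is a decrease. The test then rejects with certainty once 6 participants change, since 0.5⁶ = 0.016 is below 0.025 while 0.5⁵ = 0.031 is not. With g = 0.05 or 0.10, the probability of a significant fall ranges over s and g as follows:

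| f | N = 100 | N = 200 |
|---|---|---|
| 0.1 | 0.000 to 0.142 | 0.000 to 0.430 |
| 0.2 | 0.045 to 0.909 | 0.064 to 0.999 |
| 0.4 | 0.764 to 1.000 | 0.980 to 1.000 |
| 0.6 | 0.999 to 1.000 | 1.000 |

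A fall is close to assured when many participants come from injectable DAM, or when almost nobody starts prescribed injections. It is not assured when most come from oral DAM and some add injections.

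**4. What the companion hypothesis covers**

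A participant who replaces prescribed DAM with injected street opioids counts against the hypothesis that illicit opioid use declines. Three patterns escape it: moving from snorting to injecting at unchanged frequency, injecting a non-opioid, and new injecting among former injectable-DAM patients that is offset in aggregate by less illicit use among participants from oral DAM.

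**The case against.** The strongest defence is that the sentence should be read whole. Its safety limb is assessed partly by injections outside treatment, its last limb concerns illicit opioids, risk behaviours are a named secondary outcome, and Table 1 marks the TOP as a safety measure. The plan therefore does not ignore illicit injecting. This stands, and it limits the point to the wording of one limb.

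Prescribed injections are also a legitimate target. The Introduction and Discussion motivate the study by vein damage and abscesses, and complications of prescribed injecting are part of that. Whether the prescribed count stays low over three years, with combination and switching back allowed, is a real feasibility question. This stands too, and is a reason to keep the count as a description.

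Participants from oral DAM have no prescribed DAM injections to lose and could add some. That is correct, but mostly they contribute no change. The Introduction calls prescribing injectable DAM to non-injecting patients ethically unacceptable, so for that group g is probably near 0.

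Finally, total injections still fall by 50% to 85% in the group illustration, so a hypothesis on the total would also be met there. This is fair. The illustration shows an uninformative measure and does not demonstrate a wrong conclusion.

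Two stronger readings are tempting. A reader might infer that a patient who moves to illicit injecting is scored as a success. The documents contain no such rule: the only definition of success, in Primary outcome assessment, concerns receiving IN DAM at follow-up. A reader might also infer that the hypothesis could hardly fail. The baseline route mix is not given, and step 3 shows that the answer depends on it.

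**Conclusion.** The point holds in limited form. For participants entering from injectable DAM, a decrease in prescribed injections largely restates the prescription change that brought them into the study, and the prescribed count alone cannot show whether injecting moves outside treatment. The hypothesis is narrower than the article's own safety measure, and the hypothesis on illicit opioid use closes the gap only in part.

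The size is minor to moderate. This is one limb of a secondary hypothesis in a cohort described as exploratory, and the broader data are already planned. The numerical illustrations rest on assumed injection rates, baseline route mix and switching behaviour, none of which the article gives. The comparison of sections does not depend on them.

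**What to change.** Reconcile Study objectives and hypotheses with the safety paragraph of Secondary outcome assessment:

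- State the hypothesis as a decrease in total injection events, prescribed plus outside treatment, in the past 4 weeks among participants injecting at baseline.
- Report outside-treatment injections as a separate measure in all participants, including the proportion with new or increased outside injecting. The total alone can fall while this rises, and restricting the total to baseline injectors would miss new injectors.
- Keep prescribed injections as a description of the switch and of how far it lasts.
- Name the source of each component (dispensing records for prescribed events, self-report for the rest), so that no event is counted twice.

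The cost is wording, since both components are already to be collected. The downside is that the result becomes partly self-reported and may be less favourable than the prescribed count alone.
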